##### Patient exit interview

After completing the CAHPS, patients will be asked: 1) whether they telephoned the CIS, and if so, how many times; 2) whether any others telephoned the CIS on their behalf, and, if so whom; 3) their satisfaction with the CIS call experience; 4) other ways in which they sought information about screening; 5) whether the doctor who performed the colposcopy was their regular physician; 6) whether family members accompanied them to the visit.

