**Aim 4 **is to compare the Intervention and Usual Care groups' medical follow-up in the 6 months after abnormal Pap test notification and exit interview data at Pap test follow-up. The two outcome measures will be the dichotomous variable of timely follow-up completion (yes, no) as well as the CAHPS satisfaction questionnaire. The proportion of participants completing follow-up within 6 months will be compared between study groups using the Cochran-Mantel-Haenszel chi-square test. It is anticipated that 450 participants will consent to participation. With 225 persons per group, there is 80% power to detect a difference between a 55% appropriate follow-up rate in the control group versus a 68% rate in the intervention group. There is 99% power to detect the anticipated difference of 55% in the control group versus 75% in the intervention group.

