To compare patient satisfaction between the two groups, the four-item CAHPS scale will be used where each item is coded 1 (never, sometimes), 2 (usually) or 3 (always). The sum of these four items will have a range of 4-12. If this range represents 4 standard deviation units, then a conservatively large estimate of the standard deviation is 2 units on the CAHPS 4-item scale. Anticipated sample size for the analysis of satisfaction data (given expected follow-up rates of 55% control and 75% intervention) is 293 (control N = 124, intervention N = 169). These sample sizes have 80% power to detect an effect size of 0.34, where effect size is defined as the mean difference between intervention and control, divided by the standard deviation. With an estimated standard deviation of 2, this effect size translates into a mean difference of 0.68 (.34 × 2). With these assumptions for the sample size, the study is powered to detect a consistent difference between the groups of one response category for one item. Before the satisfaction data are analyzed, participant characteristics will be compared between the control and intervention subsamples to determine any selection bias that may have occurred due to differential follow-up between the groups. Satisfaction data will then be analyzed using a two-factor analysis of variance, with clinic (EFHC versus PAC) as one between-subjects factor and study condition (Usual Care versus Intervention) as the other. The interaction term will determine whether the intervention effect is different between the two clinics. Any demographic characteristics found to be different between the groups will be included in this analysis as covariates. Other potential covariates are whether the physician is patient's usual provider, language barrier, availability of needed translation, and whether family members accompany the patient to the appointment. The intervention by ethnicity (Hispanic vs. African American) interaction will also be tested: prior studies neither support nor negate such interaction. For all power calculations, a two-tailed test and a Type I error rate of 5% is assumed.

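### The satisfaction analysis may adjust for variables recorded at the colposcopy visit, after the letter, and names no primary model without them

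*Protocol article*

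**What the plan says.** The Primary outcomes section makes satisfaction with communication one of three primary outcomes. The Statistical analysis section analyses it by a two-factor analysis of variance, clinic by study condition, among women who attend. Covariates are then handled in two ways.

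- **Demographics.** Attenders' characteristics are compared between arms first, to look for selection caused by unequal attendance (55% control and 75% intervention expected). Then: "Any demographic characteristics found to be different between the groups will be included in this analysis as covariates".
- **Other variables.** These are listed as potential covariates, with no rule for when they enter: usual provider, plus "language barrier, availability of needed translation, and whether family members accompany the patient to the appointment".

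The timing comes from other sections. Under Intervention, the letter goes out once colposcopy has been scheduled. Under Patient exit interview, women are asked after the satisfaction scale whether the colposcopist was their regular doctor and "whether family members accompanied them to the visit". A language barrier without an interpreter is noted on the provider's checklist (Provider exit interview). Under Randomization, the Intervention letter asks the woman, or a person of her choosing, to call the Cancer Information Service.

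**The concern.** Adjusting a randomised comparison for something measured after treatment is safe only if treatment did not change it. The Intervention letter invites a second person into the information-seeking, and the exit interview asks whether others called on the woman's behalf. A relative who has been drawn in may also come to the visit, or help with translation there. If such company improves communication, it is part of how the letter works, and holding it constant removes that part from the estimate. The article leaves this adjustment open for a primary outcome and does not say which model carries the conclusion.

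The demographic rule raises a different and lesser matter. The covariate set is settled only once arm data have been compared, and a variable enters because it is imbalanced, not because it predicts satisfaction.

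**Working it through.** **Inputs from the article (Statistical analysis).** "It is anticipated that 450 participants will consent to participation", that is 225 per arm, with attendance of 55% and 75%. "For all power calculations, a two-tailed test and a Type I error rate of 5% is assumed". "These sample sizes have 80% power to detect an effect size of 0.34". "With an estimated standard deviation of 2, this effect size translates into a mean difference of 0.68".

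**Reproducing the plan.** 225 × 0.55 = 123.75 and 225 × 0.75 = 168.75, which round to 124 and 169, total 293, as stated. The standard error of the difference is 2 × √(1/124 + 1/169) = 2 × 0.1182 = 0.2365. For 0.68: 0.68/0.2365 = 2.875, and power = Φ(2.875 − 1.96) = 82.0% (81.8% by the t-test). The stated 80% is sound and not in dispute.

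**Visit-day covariate.** For a yes/no covariate that the letter shifts by a proportion s and that is worth b scale points:

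adjusted difference = 0.68 − s × b.

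The documents give neither s nor b. With b = 1.0 (0.5 SD) assumed:

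| Shift s | Adjusted difference | Share removed | Power |
|---|---|---|---|
| 0 | 0.68 | 0% | 82% |
| 5 points | 0.63 | 0.05/0.68 = 7% | 76% |
| 10 points | 0.58 | 0.10/0.68 = 15% | 69% |
| 20 points | 0.48 | 0.20/0.68 = 29% | 53% |

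Over non-zero shifts of 5 to 20 points and b from 0.5 to 1.5, the share removed runs from 0.025/0.68 = 4% to 0.30/0.68 = 44%. Least-squares simulation at 124 and 169 agrees: adjusted estimates were 0.58, 0.47 and 0.38 for (10 points, 1.0), (20, 1.0) and (20, 1.5), against unadjusted estimates of 0.67 to 0.68. The power column keeps the unadjusted standard error. With b = 1.0 a yes/no covariate explains at most 0.25 of the variance of 4, so adjustment could shrink that error by only about 3% (√(3.75/4) = 0.968).

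**Demographics chosen by test.** Simulation with five assumed covariates, each correlated 0.1 to 0.3 with the score and added if p < 0.05:

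- At least one entered in about 22–23% of trials (1 − 0.95⁵ = 22.6%).
- The mean estimate was 0.68 with and without selection.
- Type I error was 5.0% at correlation 0.1 and 3.7% at 0.3, so the test is slightly conservative.

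**Demographics and unequal attendance.** In a second simulation, a demographic correlated 0.3 with the score drove attendance in controls only, at an assumed log-odds of 0.5 or 1.0 per SD. The unadjusted estimate fell to 0.55 or 0.46. Always adjusting gave 0.68 in both cases. Adjusting only when the arms differed at p < 0.05 gave 0.63 or 0.67, because the test missed the imbalance in 54% or 10% of trials.

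**The case against.** Four points can be made for the plan.

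1. **The visit-day variables are only potential covariates.** A reader might infer that the plan commits to adjusting for them. It does not: the committed model is clinic by condition plus demographics that differ. The final choice might also be left to an analysis plan that is not shown. This limits the point to what is permitted. It does not remove it, because the article itself puts these variables forward for a primary outcome and names no primary model free of them.
2. **The four variables are not equally exposed.** A language barrier is largely a pre-existing trait, and both arms get letters in the woman's primary language. The letter follows scheduling and carries the same appointment information in both arms, so no route to who performs the procedure is documented. Treating all four as mediators goes beyond the text. Accompaniment remains, with translation as a possibility. Even for accompaniment the route is inferred, since the letter asks someone to call, not to attend.
3. **The demographic comparison has a stated purpose.** It addresses selection from 55% versus 75% attendance, and adjustment can reduce that bias, as the simulation shows. This stands. A reader might infer that test-chosen demographics also strip out the letter's effect. They cannot, because they precede the letter.
4. **No shift is documented.** This also stands. The 29% is the 20-point case at one assumed covariate effect, not an expected loss, and zero belongs in the range.

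**Conclusion.** The point holds in limited form. The article permits the primary satisfaction analysis to condition on variables recorded after the letter, chiefly accompaniment and possibly translation, and does not fix a primary model without them. With a covariate worth 1.0 point, the loss runs from 0% to 29% of the 0.68 difference for shifts of 0 to 20 points, and power from 82% to 53%. These figures assume that the letter raises the covariate and that the covariate raises satisfaction. With opposite signs, the same formula would enlarge the estimate instead. If the letter changes nothing, nothing is lost.

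The demographic rule is a weakness of pre-specification only. It leaves the estimate unbiased on average in the simulated setting without selective attendance, and some demographic adjustment is desirable because only attenders are analysed. The case is for fixing that adjustment in advance, not for dropping it.

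**What to change.** - **Primary model:** name it in advance as condition, clinic and a fixed set of demographics known before mailing, included whether or not they differ between arms. Examples are age, primary language and, if recorded, ethnicity. Age is needed for the entry criteria and language for choosing the letter; that ethnicity is recorded for each woman is an assumption.
- **Selection check:** keep the comparison of attenders' characteristics as a description of selection. Adjust for any further demographic found imbalanced as a sensitivity analysis, not as a change to the primary model.
- **Visit-day variables:** move usual provider, language barrier, translation and accompaniment to an exploratory analysis labelled as such.

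The cost is wording, a little more analysis work, and less freedom to choose covariates after seeing the data. Sample size and data collection are unchanged if the chosen demographics are already recorded.

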## Discussion

The present study will develop and test the efficacy for enhancing calls to the CIS, timely colposcopy, and satisfaction with provider-patient communication of a targeted physician mailing. The mailing is designed to connect the CIS to low-income African-American and Hispanic women who need information about abnormal Pap tests and colposcopy. The study has the potential to identify a low-cost, feasible, effective, sustainable, and culturally sensitive strategy to increase awareness of the CIS and use of its free cancer information services among an underserved population. In addition to rigorous efficacy testing of the intervention during the experimental phase of the research, the study will examine other aspects of feasibility such as acceptability, and demand [51]. The formative phase of the research evaluates the acceptability of the intervention via focus groups that ask patients and providers about the design and perceived usefulness of the proposed targeted physician mailing. Calls to the CIS from patients participating in the study, a primary outcome in efficacy testing, also can be interpreted as a measure of demand for the intervention among the target population. In this study, demand will be assessed both by self-reported calls and calls recorded by the CIS.

By testing a feasible intervention in real-life settings of practice (the clinics) and public service (the CIS), and by evaluating different aspects of feasibility, the ACCISS study aims to bridge a gap between research and practice. So few trials on the efficacy of cancer prevention and control interventions have been tested under real-world conditions so as to suggest to some that randomized controlled trials have low applicability to public health settings [52-54]. The ACCISS study proceeds from the premise that high quality randomized controlled trials can be implemented quite feasibly in a real world setting. Indeed, we suggest that it would be inequitable to test interventions intended for underserved populations using research designs less internally valid than those used to test interventions intended for majority populations. Patients, providers, and CIS staff all will participate in the development of the intervention to ensure its acceptability, culturally sensitivity, and sustainability. Making dissemination potential and practice integration a priority from the inception of the research, CIS and clinic representatives were involved in the development of the proposal for funding. Finally, the inclusion of adherence and patient satisfaction as primary outcomes is congruent with recommendations to include multiple, clinically relevant outcomes in practical clinical trials [52,55]. The research follows these foundational principles so that, if proven effective, the ACCISS intervention can be sustained and referrals to the CIS can be incorporated into clinical practice. CIS is well positioned to enhance and supplement cancer-related information provided in primary care settings in a manner that benefits both patients and health care providers. CIS's status as part of the National Cancer Institute, addresses potential provider concerns regarding quality of the information provided by a third party. By offering information in one-on-one interactions with specialists well- trained in the interpersonal as well as informational aspects of cancer communication, CIS has potential to invoke trust among underserved patients who as a rule prefer to receive health information verbally [14,19].

CIS is also favorably positioned to partner in the complex endeavor of research. Although it is first and foremost a service organization, CIS has its own research program complete with a research agenda dedicated to bridging the gap between research and service [4]. CIS staff is trained to conduct research studies embedded in the service environment. From the perspective of CIS, this study is a model of collaboration. The research engages CIS with academic researchers and public health clinics in a mutually beneficial collaboration that strives to produce health benefits for the underserved.

While the study has considerable strengths, it also has limitations. First, in the clinics and within the CIS, practice/service takes priority over research. Therefore, extra effort will be required to integrate research into daily practice and service activities in a manner that ensures correct implementation of data collection processes. Second, a primary outcome, calls to the CIS, will be measured via patient self-report as well as via calls recorded by CIS as coming from the study. Because CIS calls are anonymous, call information cannot be used to verify self-report or vice versa.

These limitations notwithstanding, the present study has the potential to connect the CIS to low-income patients who need cancer screening information. By doing so, the study may contribute to overcoming communication barriers that underlie cancer health disparities.
